### **12.4.2 Analysis of Secondary Endpoints**

We will examine summary statistics, histograms, and scatter plots of the measured covariates and outcomes for outliers and data trends. Analyses of differences between those completing and not completing the study and the within-group changes during the intervention will be performed according to modified intention-to-treat principles. Multivariate linear regression (MLR) models will be used to examine the relationship between changes in the social network processes and exposure (the social network lifestyle intervention vs the lifestyle intervention), adjusted for covariates selected from univariate analyses; potential covariates for MLR are categorized by theoretical construct. We will also explore the effect of gender by including a three-way interaction (gender*social support*weight loss), although we recognize that we might not have enough power to detect such interactions.

To further explore the effect of the intervention, we will do sensitivity analysis: (1) Multivariable linear regression using weight loss as continuous outcome variables (a change in weight and percent weight change), adjusting for baseline covariates distributed differently between intervention groups; (3) test interaction terms between treatment group and other covariates; and (4) examine completers only.

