# 1. Protocol Summary

Full Title: Reducing OBesity Using Social Ties (ROBUST): Randomized Controlled Trial Short Title: ROBUST- RCT

Clinical Phase: III

Principal Investigator: [name], MS

**Study Description:** Randomized controlled trial comparing two behavioral weight-loss interventions; a social-network enhanced lifestyle intervention (Intervention group) and an individual level lifestyle intervention (Control group), among Black and Hispanic adults with obesity over the course of 24 weeks. This study aims to test the feasibility and acceptability reforming interpersonal barriers and addressing social network barriers to behavior change, by engaging social network members in a lifestyle intervention for weight loss compared to the lifestyle intervention alone.

**Sample Size:** *N=* *66 (Intervention index participants)*

*N=132 (Intervention Social Network members)*

*N= 66 (Control participants)*

*N=264 (Total Sample Size)*

**Enrollment:** In the intervention group, this study will enroll 66 index participants and 132 social network member subjects. In the control group, this study will enroll up to 66 index participants.

**Study Population:** Individuals who self-identify as Non-Hispanic Black or Hispanic adults 18 years of age or older with a calculated BMI ≥ 30 kg/m2

**Enrollment Period:** *24 weeks*

**Study Design:** Randomized controlled trial comparing a social-network enhanced lifestyle (intervention group) to an individual-level lifestyle intervention (control group). Subjects in both arms (n=66 each) will receive the same number of behavioral coaching sessions (15 total) with four sessions conducted in person (baseline, week 8, week 16, and week 24), and the remaining 11 sessions conducted virtually. Subjects randomized to the social network intervention will nominate up to a maximum of two members of their social network (n=132) who will also be consented at baseline, complete a brief baseline interview, and attend the virtual coaching sessions with the randomized subject at weeks 3, 5, and 15. The social network members will also complete a close-out study interview at week 24.

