### **1.2.5 Secondary Endpoints**

Increase in positive communication and problem solving scores on the McMaster Family Assessment Device (FAD) for the participant and their social network members.

Decrease in social norms that promote unhealthy eating and physical inactivity (unhealthy weight norms).

Increase in participant physical activity, and decrease in caloric intake.

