## 7.11 Measures to Minimize Bias: Randomization and Blinding

Index participants will be randomized after completion of the social network interview either to the ROBUST intervention or lifestyle intervention, using a random number generator. All index participants, regardless of randomization group, will complete a social network interview to characterize their personal network prior to randomization. The same social network interview will be conducted at 24 weeks. All participants will also receive the same number of coaching sessions, as shown in **Table 1**. They will attend four sessions in person (baseline, week 8, week 16, and week 24), and the remaining 11 sessions will be conducted as a virtual visit. The in-person visits will occur at the Weill Cornell Clinical and Translational Science Center's dedicated research facility. During the in-person sessions, the participant will receive 1:1 dietary counseling with a registered dietician who has been trained on the study protocol. The study research staff complete anthropometric measurements (height, weight, and body composition). Participants randomized to the intervention group will be expected to attend virtual visits at weeks 3, 5, and 15 with their social network member.

Consenting of study participants as well as all study assessments (i.e. baseline, 8 ,16 & 24 weeks) will be conducted by an assessor who is not responsible or involved in the delivery of the coaching sessions, dietary counseling or communication skills sessions. While the study PI & co-investigators will be blinded, the same will not be possible for the trained coach delivering the intervention. Due to budget limitations, having two coaches (i.e. one for the control group and for the intervention group) is not feasible. Since the communication skills training sessions are designed to occur between the index participant and consented social network members, the implication of contamination is reduced as control group participants will not have any consented social network members participating in the study.

*.*

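### The physical activity and calorie endpoint names no comparator, and the only inferential analysis stated that could cover it is a within-group change

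*Protocol*

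**What the plan says.** Section 1.2.5 of the protocol, repeated in the Protocol Summary, lists three secondary endpoints, each worded as a direction of change with no reference to the control arm:

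- The behavioural endpoint, which is the main subject here, reads "Increase in participant physical activity, and decrease in caloric intake".
- The endpoint on norms reads "Decrease in social norms that promote unhealthy eating and physical inactivity (unhealthy weight norms").
- The third asks for higher communication and problem-solving scores on the FAD, in index participants and in network members.

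Section 12.4.2 sets out the analysis. After summary statistics and plots, it says that completer versus non-completer differences and "the within-group changes during the intervention will be performed according to modified intention-to-treat principles". It then says: "Multivariate linear regression (MLR) models will be used to examine the relationship between changes in the social network processes and exposure", where exposure is the randomised arm. A second regression, listed under sensitivity analysis, has weight change and percent weight change as outcomes. Section 10.1 adds only summary statistics and plots for the secondary objective.

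On the control condition, the Protocol Summary says: "Subjects in both arms (n=66 each) will receive the same number of behavioral coaching sessions (15 total". Section 6.1.2 makes all sessions the same in both arms except weeks 3, 5 and 15, when the control arm has ordinary coaching in place of communication skills training.

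**The concern.** The trial asks whether involving network members adds anything to lifestyle coaching. The secondary objectives in section 1.2.2 are worded accordingly: they ask about the impact of ROBUST, and whether better network processes lead to greater uptake of healthy diets and activity. A change within the ROBUST arm answers a different question. It combines the coaching that both arms receive, regression to the mean, the effect of time, and any network effect. With an active control arm the first of these may be substantial.

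If the endpoint is read as worded and analysed by the one stated method that could cover it, it can be reported as met with no difference between the arms. The protocol also says, under Stopping rules in section 15, that the trial should supply estimates for a larger study. A within-arm change is not the estimate such a study would need.

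**Working it through.** **1. Which stated analysis covers which endpoint**

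- Norms: section 3.1 lists the key network processes as communal coping, social norms and affect. Norms therefore fall under the arm regression in 12.4.2.
- Index participants' communication and problem-solving scores: arguably part of communal coping, and so arguably under the same regression.
- Network members' scores: no arm comparison is possible, because section 7.11 says "control group participants will not have any consented social network members participating in the study".
- Physical activity and caloric intake: not among the processes in section 3.1, and not weight. The later sensitivity items (interactions, completers only) name no outcome. What remains is summary statistics, the completer comparison, and the within-group analysis.

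The data for an arm comparison are planned. The schedule in section 6.1 has activity and three-day food records for index participants at weeks 0, 8, 16 and 24.

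**2. The protocol's own power figure**

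Section 15 gives 98% power for an 8-pound difference between arms (SD 10.4) with 132 participants and 15% attrition. It gives 96%, 92% and 88% at 30%, 40% and 50% dropout. The significance level is not stated; I assume two-sided 5%.

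Power = Φ(δ / (σ√(2/n)) − 1.96)

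- 15%: n = 66 × 0.85 ≈ 56 per arm; 8 / (10.4 × √(2/56)) = 4.07; Φ(2.11) = 98.3%
- 30%: n = 46; 95.8%
- 40%: n = 39; 92.5%
- 50%: n = 33; 87.8%

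The figures reproduce. They concern a between-arm contrast for weight, which is not in the section 1.2.5 list, so they do not cover activity or calories.

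**3. Illustration of the gap between the two contrasts**

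Assumptions, none of them in the protocol except the 56 per arm: the standardised within-person change dz is equal in both arms, so the true arm difference is zero; paired t test in the ROBUST arm; two-sided 5%, counting only results in the desired direction.

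The non-centrality is dz × √56 = 7.483 × dz, with 55 degrees of freedom.

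| dz | non-centrality | within-ROBUST test significant |
|---|---|---|
| 0.2 | 1.50 | 31% |
| 0.3 | 2.24 | 60% |
| 0.4 | 2.99 | 84% |
| 0.5 | 3.74 | 96% |

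A two-sided 5% between-arm test would favour ROBUST in 2.5% of the same trials, whatever dz is.

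If the endpoint is taken literally, so that any mean change in the right direction counts, the chance is Φ(7.483 × dz): 93% at dz 0.2 and about 99% at 0.3. By symmetry, a between-arm point estimate would favour ROBUST in 50%.

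**The case against.** The strongest reply is that the gap is inferred. The within-group sentence names no outcome, and nothing says that activity and calories will be judged on it alone. Endpoints worded as a direction of change are common shorthand in a two-arm trial. The trial is described throughout as a randomised comparison, the secondary objectives are comparative in tone, and section 15 powers a difference between arms. Naming the model for each secondary endpoint is often left to the statistical analysis plan. The sensitivity list in 12.4.2 also runs (1), (3), (4), so an item may be missing.

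Much of this stands. A comparison was probably intended, and the point is no evidence of an intention to rely on within-group tests. What remains is that the protocol is not silent. It fixes the endpoint as an uncontrolled change, states a within-group analysis, and assigns arm comparisons to other named outcomes. An analysis plan that followed this text faithfully would keep the gap. A missing sensitivity item, whatever it held, would not supply the main analysis.

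A reader might infer more than the text supports:

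- That all secondary endpoints lack an arm comparison. Norms, and arguably index participants' communication and problem-solving scores, have one in 12.4.2; for these only the endpoint wording is incomplete.
- That both arms get the same sessions. They get the same number; content differs at weeks 3, 5 and 15.
- That 60% to 96% is the false-positive rate of a planned test. The protocol states no significance level, no within-arm test for this endpoint and no rule for calling it met.

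**Conclusion.** The point holds for physical activity and caloric intake in index participants. The endpoint names no comparator, no between-arm analysis is stated for it, and the within-group change cannot separate the network component from coaching common to both arms. For norms and index participants' communication and problem-solving scores, the fault is only in how the endpoints are worded.

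The size is illustrative. With no true arm difference, 56 per arm, two-sided 5% and an assumed equal standardised change of 0.3 to 0.5, a within-ROBUST test is significant in about 60% to 96% of trials, against 2.5% for a between-arm test in ROBUST's favour. A smaller shared change narrows the gap: 31% at 0.2.

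It should be fixed before outcomes are analysed, so that the result does not choose the contrast. It is not critical: the endpoint is secondary in a feasibility trial, and no primary criterion depends on it.

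**What to change.** In sections 1.2.5 and 12.4.2, and in the Protocol Summary:

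- State the index-participant activity and calorie endpoints as the ROBUST-minus-control difference at week 24, estimated by a linear model with arm and the baseline value.
- Word the norms endpoint and the index-participant FAD endpoint as between-arm differences too, in line with the arm regression already in 12.4.2.
- Label within-group changes descriptive only. Do the same for network members' changes, which have no control counterpart.

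The choice of analysis set is a separate matter and need not change for this fix.

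The cost is wording and one regression per endpoint. Activity and diet data are already scheduled in both arms. The schedule table in section 6.1 does not name the FAD, so its collection in both arms should be confirmed. The small downside is that some endpoints a within-group test would call met may no longer be met.

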### **6.1.2 Treatment Phase**

Eligible participants will be randomly assigned to the social network intervention or control groups in a 1:1 ratio using a numerical randomization scheme developed by the statistical team. Following randomization, participants that are randomized to the social network intervention group will complete 3 in person communication skills sessions with their social network members during weeks 3, 5, and 15. Instead of completing communication skills sessions, participants randomized to the control group will complete regular virtual lifestyle coaching sessions with the study team that consists of the following topics: Keep your health healthy (week 3), Eat well away from home (week 5), and Social Cues (Week 15). All other sessions will focus on the topics below and will be the same across both treatment groups.

Note: The weeks that are not listed in the treatment phase below are weeks that will be treatment breaks.

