## Stopping rules

In this minimal risk lifestyle intervention trial, it is more likely that difficulty in recruiting adequate numbers of participants will require stopping the trial than that excess adverse events will occur and require stopping the trial. However, as outlined elsewhere, we will monitor injury rates in all participants and the safety officer, together with the study investigators, will alert the IRB and the NIH if a larger than reasonably expected event rate should occur in the treatment group. Other issues relating to stopping rules for this trial include:

New Information

It is exceedingly unlikely that any new information will become available during this trial that would necessitate stopping the trial.

Limits of Assumptions

It is possible that baseline differences between the groups, excessive study dropouts and/or missing data by the interim measurement time point will limit the value of data analysis of measurements at the 3-year time point. Baseline differences will be evaluated after the first measurement time point. Given the monitoring plans outlined elsewhere in this document, it is exceedingly unlikely that there will be baseline differences between groups of any magnitude to threaten the validity of the study.

While this R01 mechanism's primary aim is to determine the feasibility and acceptability of the intervention our goal is also to obtain appropriate estimates for a larger trial. Based on a sample size of 132 participants with an expected attrition of 15% we will have sufficient power (98%) to detect an 8-pound difference SD 10.4) between the intervention and control group (secondary outcome). Alert points are set at dropout rates of 30% (low alert), 40% (mid-alert), and 50% (high alert). As shown in the table below even at a high level alert we will still have moderate power (0.87) to determine our secondary outcomes.

| Dropout Rate  Alert level | 30%  low | 40%  mid | 50 %  high |
| --- | --- | --- | --- |
| Power available | 96% | 92% | 88% |

The actions taken at each level of alert are given below:

Low to mid-level alert = Conference call between study investigators to discuss approaches to minimize further losses to follow-up/dropouts.

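### Section 12.4.2 picks covariates from the trial's own data and requires no baseline value of the outcome, and 24-week weight loss, the powered secondary outcome, has only a sensitivity analysis

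*Protocol*

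**What the plan says.** Protocol section 12.4.2 plans two kinds of between-arm linear regression.

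- **Network processes.** Changes in these processes are regressed on arm, "adjusted for covariates selected from univariate analyses; potential covariates for MLR are categorized by theoretical construct". No selection threshold is given, and the text does not say whether the baseline value of the outcome is among the candidates.
- **Weight.** Change and percent change in weight are regressed on arm, "adjusting for baseline covariates distributed differently between intervention groups". This is item (1) of a list headed as sensitivity analysis. No other between-arm model for weight is described.

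Table 1 in section 6.1 schedules week-0 values in index participants for weight, support and undermining, norms, communal coping, physical activity and diet.

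The status of weight differs by section. Section 1.2.2 includes weight loss at 24 weeks in a secondary objective. The Stopping rules part of section 15 claims "sufficient power (98%) to detect an 8-pound difference SD 10.4) between the intervention and control group (secondary outcome") and ties its dropout alerts to that calculation. The endpoint list in section 1.2.5 does not include weight; its last entry is "Increase in participant physical activity, and decrease in caloric intake".

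**The concern.** Two things look wrong.

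1. **Covariate choice.** Both rules settle the model only after outcome or arm data have been seen. Under randomisation "control groups in a 1:1 ratio", an observed baseline imbalance is a chance event and says nothing about whether the covariate is prognostic. The covariate most likely to be prognostic for a change score is the outcome's own baseline, and it enters only if it happens to pass a screen. The Stopping rules text names estimates for a larger trial as a goal. An estimate whose adjustment set was chosen from the same data serves that goal poorly.

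2. **Status of weight.** The one outcome with a stated effect size, SD and power has no main analysis. A sensitivity analysis needs a main analysis to be compared with, and none is given for weight.

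**Working it through.** **Step 1. Reproduce the plan's power.** Inputs from Stopping rules: "Based on a sample size of 132 participants with an expected attrition of 15" per cent, difference 8 lb, SD 10.4. Allocation is 1:1, so n per arm = 66 × (1 − dropout). The protocol states no alpha; two-sided 0.05 is assumed. The test statistic has mean 8 / (10.4 × √(2/n)); power is taken from the normal approximation and from the noncentral t.

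| Dropout | n per arm | Mean of statistic | Normal | t | Stated |
|---|---|---|---|---|---|
| 15% | 56.1 | 4.07 | 98.3% | 98.1% | 98% |
| 30% | 46.2 | 3.70 | 95.9% | 95.5% | 96% |
| 40% | 39.6 | 3.42 | 92.8% | 92.2% | 92% |
| 50% | 33.0 | 3.13 | 87.8% | 86.8% | 88% (table), 0.87 (text) |

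The stated figures reproduce.

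**Step 2. Value of baseline adjustment.** Let rho be the correlation between baseline and week 24, with equal variances (SD 1) at both times. The documents give no rho, so a range is shown. The variance of a change score is 2(1 − rho); after baseline adjustment it is 1 − rho². The ratio is (1 + rho)/2, a variance reduction of 30%, 20% and 10% at rho 0.4, 0.6 and 0.8.

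For 56 per arm and an effect of 0.4 SD, √(2/56) = 0.189. Approximate power is Φ(0.4/SE − 1.96):

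| rho | SE, change score | Power | SE, baseline-adjusted | Power |
|---|---|---|---|---|
| 0.4 | 1.095 × 0.189 = 0.207 | 49% | 0.917 × 0.189 = 0.173 | 64% |
| 0.6 | 0.894 × 0.189 = 0.169 | 66% | 0.800 × 0.189 = 0.151 | 75% |
| 0.8 | 0.632 × 0.189 = 0.120 | 92% | 0.600 × 0.189 = 0.113 | 94% |

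**Step 3. Effect of the selection rules.** Simulation with 112 analysed, effect 0.4 SD, 15 candidate covariates and selection at p < 0.10. The number of candidates, the threshold and the effect are assumptions. Power:

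| Rule | rho 0.4 | rho 0.6 | rho 0.8 |
|---|---|---|---|
| Prespecified baseline adjustment | 65% | 75% | 94% |
| Univariate screen, baseline a candidate | 63% | 74% | 92% |
| Univariate screen, baseline not a candidate | 47% | 64% | 89% |
| Imbalance rule | 47% | 64% | 89% |

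Repeat runs differ by a few points (baseline adjustment at rho 0.4 ranged from 62% to 65%), but the pattern is the same. Type I error stayed at about 4 to 6% under every rule.

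The second and third rows differ for a simple reason. Baseline correlates with change at −√((1 − rho)/2), which is −0.55, −0.45 and −0.32. If it is offered to the screen it is nearly always selected: in 100%, 100% and 95% of runs. If it is not offered, the screen has nothing prognostic to find. Section 12.4.2 does not say which case applies.

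**Step 4. Weight.** If 10.4 lb is the SD of weight change, the baseline-adjusted SD is 10.4 × √((1 + rho)/2). At rho 0.9 this is 10.14 and power at 15% dropout is 98.5%, against 98.1% unadjusted. At rho 0.7 it is 9.59 and 99.2%. The gain is small.

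**Step 5. Status of weight.** Section 1.2.2 makes it part of an objective; Stopping rules makes it the secondary outcome; section 1.2.5 omits it; section 12.4.2 gives it a sensitivity analysis. The four places do not agree.

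**The case against.** The best defence is that a univariate screen would almost always pick up the baseline value, so the network-process models would end up close to what is recommended here. That stands if baseline is in the candidate pool. A reader might infer from the first part of the concern that univariate selection always costs 10 points or more of power; the documents do not support that, because they do not exclude baseline from the pool. The full loss applies to the imbalance rule, which the plan uses only for weight, where rho is probably high and power is ample.

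Other stronger readings also fail.

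- **Inflated false positives.** The simulations show none.
- **Adjustment for post-baseline mediators.** Candidates are grouped by construct, and some constructs are intervention targets, but nothing says post-baseline values will be entered. The weight model says baseline, and Table 1's personal construct includes ordinary baseline items such as age, sex and education.
- **Weight has no standing.** It is in a stated secondary objective and is called the secondary outcome. Section 1.2.2 does frame it as a consequence of network changes and not as a direct arm comparison, but Stopping rules powers exactly that arm comparison.
- **A week-0 value for every endpoint.** The visible schedule does not name the McMaster Family Assessment Device, and Appendix A is a figure not shown, so this cannot be confirmed.

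Finally, feasibility is the primary aim, so these are secondary analyses. That limits the weight of the point. It does not remove it: the protocol fixes these selection rules itself, so a statistical analysis plan naming covariates in advance would contradict section 12.4.2.

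**Conclusion.** The point holds in a limited form and is worth changing, though it does not threaten the trial. Both covariate rules depend on the trial's data, and neither guarantees adjustment for the outcome's baseline. The certain cost is an estimate that is not prespecified. The cost in power depends on a choice the protocol leaves open: about 1 to 2 points if baseline is a candidate in the univariate screen, and about 18, 11 and 5 points (65 − 47, 75 − 64, 94 − 89) at rho 0.4, 0.6 and 0.8 if it is not. These figures rest on assumed correlations, equal variances, 112 analysed and a 0.4 SD effect. The stated 98% power for weight is right, so sample size is not in question. For weight the problem is its inconsistent status across sections 1.2.2, 1.2.5, 12.4.2 and Stopping rules, which needs no simulation to establish.

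**What to change.** - **Model.** For each continuous secondary outcome with a week-0 value, regress the week-24 value (or the change, which gives the same arm effect once baseline is in the model) on arm, that outcome's baseline value, and any further baseline covariates named in section 12.4.2 before the data are seen.
- **Selection rules.** Delete both the univariate screen and the choice by observed imbalance.
- **Weight.** Add 24-week weight change to section 1.2.5, make the model above its main analysis, and keep the sensitivity label for variants of it, such as completers only.
- **Optional.** A mixed model could be used for measures taken at weeks 0, 8, 16 and 24. It addresses missing visits, which is a separate matter.

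The cost is protocol wording. No new data are needed for the outcomes with a week-0 value in Table 1. For the Family Assessment Device, first confirm that a baseline assessment is scheduled.
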